### Blinding

It is not possible to blind participant mothers because the experimental treatment condition teaches mothers specific skills to reduce distress and interact sensitively with their infants, while mothers in the control group receive non-specific attention. However, we tell both groups that their intervention *may *reduce anxiety and distress, in order to minimize any differences in participants' expectations.

Careful attention is paid to the blinding of assessors and data collectors. All pre-intervention data are obtained blinded because they are collected prior to randomization. The research assistants who collect the post-intervention data (1 & 6 months of age) are not involved in the pre-intervention data collection. Research assistants are instructed not to ask participants about their group assignment, and participants are asked not to reveal their group assignment to research or medical staff. Mothers read and respond to self-report questionnaires independently. The research assistants who videotape interactions in the home are not involved in the coding of the videotapes. All interaction videotapes are coded at a later date by a research assistant hired just for this task, and who has no contact with the NICU or with participants and thus is blind to group assignment. Other staff, also blind to group assignment, are trained to score the NBRS via chart review. Finally, post-intervention research assistants and interveners are housed in separate buildings to minimize the chance of information transfer, and there are separate meetings for interveners and other research staff.

### Contamination

Contamination is a potential concern when delivering an intervention to mothers in NICUs, which are large open units, with infant incubators located in close proximity to one another. Inevitably, there is interaction between mothers. In order to address this issue, we have adopted inclusion/exclusion criteria that preclude the recruitment of mothers who are sharing a room. Once participants are enrolled in the study, we employ several strategies to deal with contamination. First, we explain to participants that we can only test the effectiveness of the intervention if they do not share information. Second, interveners are instructed not to discuss the program content with non-participants or with NICU staff. Third, whenever possible, interveners deliver the intervention sessions at a private location where their discussion cannot be overheard by other mothers or NICU staff. Fourth, when sessions take place at the infant's bedside, the interveners place a screen around the bedside to maximize privacy. Fifth, when the intervention is completed we ask mothers if they have shared any of the program information with other NICU mothers, and if so with whom. Finally, we measure contamination post-intervention by asking mothers in both the experimental and control groups to respond to a questionnaire testing their knowledge of the content of both programs and to indicate the source of this knowledge.

### Planned analyses

No interim analyses are planned. Upon completion of the study, we will compare baseline values for demographic variables to assess the adequacy of randomization. These include maternal age, education, parity, psychosocial services used by the mother, and infant illness severity. The primary outcome is the difference in STAI scores between the intervention group and the control group, evaluated immediately post-intervention. This is a continuous measure and will be analyzed using an unpaired t-test (i.e. comparison of scores between two independent samples) and an intent-to-treat strategy. The overall significance level will be considered at a two-sided 0.05 level. As a secondary analysis, we will use a multiple regression model to account for other predictors of outcome, including baseline STAI, and the demographic variables noted immediately above. Finally, as an exploratory analysis, we will compare groups based on actual treatment received in addition to our primary intention-to-treat analysis. The analysis of secondary measures will proceed in a likewise fashion. We will also report on contamination and describe other services used during and after the intervention. Because we only have 46 subjects per group, we cannot use sophisticated multiple imputation techniques to estimate expected results in subjects who withdraw from the study. Therefore, we will document and describe the reasons for attrition within each group, but exclude these subjects from the multiple regression analyses.

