Power analysis was based on the work of Mohide [52], which indicated that a change of 7 points on the STAI scale (the primary outcome) is considered clinically meaningful. Setting alpha = 0.05 and power = 0.8, we would need 40 subjects per group [53]. To account for attrition, a sample of 46 mothers per group will be recruited.

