### Procedures

The study timeline can be found in Figure 1. Following recruitment, informed consent is obtained, and baseline measures (STAI, PPQ, and EPDS) are administered. Participants are then randomized to either the Cues or the Care condition. Within a day of randomization, an intervener contacts the participant and arranges for the first session of the intervention.

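### The primary STAI comparison is an unadjusted t-test although baseline STAI is collected before randomization; baseline-adjusted ANCOVA should be primary

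*Protocol article*

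**What the plan says.** The Planned analyses section of the protocol article defines the comparison: "The primary outcome is the difference in STAI scores between the intervention group and the control group, evaluated immediately post-intervention". On method it states: "This is a continuous measure and will be analyzed using an unpaired t-test", by intention to treat, and on the error rate: "The overall significance level will be considered at a two-sided 0.05 level".

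The Procedures section gives the order of events after consent: "baseline measures (STAI, PPQ, and EPDS) are administered. Participants are then randomized to either the Cues or the Care condition". A pre-randomization value of the primary measure is therefore planned for every mother.

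That value is used in one place only (Planned analyses): "As a secondary analysis, we will use a multiple regression model to account for other predictors of outcome, including baseline STAI". The other predictors in that model are maternal age, education, parity, psychosocial services used and infant illness severity. Secondary measures are to be analysed in the same way.

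The sample size (Participants section) rests on the statement that "a change of 7 points on the STAI scale (the primary outcome) is considered clinically meaningful", followed by: "Setting alpha = 0.05 and power = 0.8, we would need 40 subjects per group". Forty-six per group are to be recruited to allow for attrition. Neither an SD nor a baseline-to-outcome correlation is given.

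**The concern.** The same scale is completed by the same mothers before and after the intervention, so baseline STAI is the obvious prognostic covariate. Leaving it out of the deciding analysis has two consequences.

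- **Precision.** Any outcome variation that baseline anxiety explains stays in the error term, so the confidence interval is wider than it need be. With about 40 analysable mothers per group this can matter.
- **Chance imbalance.** Randomization is stratified by hospital only, so baseline anxiety is not balanced by design. The planned check of baseline comparability lists demographic variables, service use and illness severity, but not STAI. If the groups differ by chance on baseline anxiety, a fraction of that difference equal to the regression slope of outcome on baseline carries into the unadjusted estimate.

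The secondary regression does not repair this, because it does not carry the confirmatory conclusion. It is also not a simple baseline-adjusted comparison. It adds several other covariates, one of which (the NBRS, for infant illness severity) is scored at discharge, after randomization and after most sessions, according to the Additional variables section. The PPQ, a secondary outcome that also has a pre-randomization value, inherits the same ordering of analyses.

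**Working it through.** **Inputs from the protocol article:** difference 7 points, alpha 0.05, power 0.80, 40 per group (Participants); two-sided test (Planned analyses).

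**Assumed, because not stated:** the STAI SD, back-solved below and taken to be equal at baseline and follow-up; and the correlation r between baseline and post-intervention STAI, varied from 0.2 to 0.7.

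**1. The plan's own figure.** Without an SD, 40 per group cannot be reproduced independently, so it is solved backwards.

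- Normal approximation: SD = 7 / [(1.960 + 0.842) × √(2/40)] = 7 / 0.626 = 11.17.
- Exact two-sample t-test: standardized difference 0.634, so SD = 7 / 0.634 = 11.04.

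An SD of 11.0 to 11.2 with no baseline adjustment returns 39 to 41 per group. The planned sample size therefore takes no credit for baseline STAI.

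**2. ANCOVA with the same 40 per group.** Residual SD = SD × √(1 − r²), SE = residual SD × √(2/40), power = Φ(7/SE − 1.960), n per group for 80% power = 40 × (1 − r²), detectable difference at 80% power = 2.802 × SE. With SD 11.17:

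| r (assumed) | Residual SD | SE | Power | n per group for 80% | Detectable difference |
|---|---|---|---|---|---|
| 0 (unadjusted) | 11.17 | 2.50 | 80.0% | 40.0 | 7.0 |
| 0.2 | 10.95 | 2.45 | 81.6% | 38.4 | 6.9 |
| 0.3 | 10.66 | 2.38 | 83.6% | 36.4 | 6.7 |
| 0.5 | 9.68 | 2.16 | 89.9% | 30.0 | 6.1 |
| 0.7 | 7.98 | 1.78 | 97.5% | 20.4 | 5.0 |

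Example at r = 0.5: 11.17 × √0.75 = 9.68; 9.68 × √(2/40) = 2.16; 7/2.16 − 1.96 = 1.27; Φ = 0.899.

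The noncentral t with SD 11.04 and 77 degrees of freedom also gives 83.6%, 89.9% and 97.5% at r = 0.3, 0.5 and 0.7.

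**3. Cost if baseline is uninformative.** At r = 0 the only loss is one degree of freedom: power 79.99% against 80%.

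**4. Chance imbalance.** The SE of the baseline mean difference is 11.17 × √(2/40) = 2.50 points (2.47 with SD 11.04). With equal SDs, a one-SE imbalance shifts the expected unadjusted difference by r × 2.50:

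- r = 0.3: 0.75 points, 11% of the 7-point target
- r = 0.5: 1.25 points, 18%
- r = 0.7: 1.75 points, 25%

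**The case against.** The strongest reply is that nothing here is invalid. In a randomized comparison the unpaired t-test is unbiased over repeated randomizations and keeps its type I error. Its standard error already allows for chance imbalance on average. It also matches the sample size calculation, so the trial gets the power it planned for. A baseline-adjusted model is pre-specified as secondary, and the ranking of the two analyses is clear in advance. All of this stands, and it is why the point concerns efficiency rather than validity.

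The size of the gain is also uncertain. The outcome is the state scale, which asks about feelings at the time of completion. Five sessions at one or two per week take about 2.5 to 5 weeks, the home session comes 2 to 4 weeks after discharge, and assessment 2 to 3 weeks after that. The two measurements are thus some 6.5 to 12 weeks apart, plus any wait for discharge, and the setting moves from NICU to home. The correlation could be modest, and nothing in the document supports 0.7 in particular. At 0.2 the gain is only 1.6 percentage points of power.

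None of this points to a disadvantage of adjusting: the worst case is one degree of freedom. Nor does a secondary model do the work of a primary one. If the two results differ, the plan lets the usually less precise one decide.

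**Conclusion.** The concern holds, and the change should be made. The unadjusted t-test is a valid but inefficient choice for the deciding analysis, given that baseline STAI is collected anyway. For assumed correlations of 0.3 to 0.7 the gain is about 4 to 18 percentage points of power at 40 per group, equivalent to needing about 36 down to about 20 or 21 per group. At 0.2 or below it is under 2 points. The direction of the benefit is secure. Its size is not, because it rests on an SD back-solved from the sample size and on a correlation that the document does not give.

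**What to change.** Before outcome data are examined, make the primary analysis a linear regression (ANCOVA) of post-intervention state STAI on treatment arm and baseline state STAI. Hospital, the stratification factor, can reasonably be added. Report the adjusted mean difference with its 95% confidence interval, and keep the unpaired t-test as a supportive analysis. Apply the same model to the PPQ with its own baseline. State how a missing baseline STAI will be handled.

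The change takes a sentence or two in Planned analyses. It needs no additional data or participants and costs one degree of freedom for baseline STAI, plus one more if hospital is included.

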**Figure 1 F1:**
[figure not shown]
**Cues and Care Trial timeline**. STAI = State TraitAnxiety Inventory. EPDS = Edinburgh Postnatal Depression Scale. PPQ = Perinatal PTSD Questionnaire. PSS-NICU = Parent Stressor Scale: Neonatal Intensive Care Unit. BSID-III = Bayley Scales of Infant Development-third edition.

Post-intervention measures are administered at the participant's home 2 – 3 weeks after the intervention ends (when infants are 1 – 1.5 months corrected age). This assessment includes observation of mother-infant interaction, and completion of the self-report measures of anxiety, depression, and posttraumatic stress. In addition, participant mothers are asked to report on their satisfaction with the intervention that they received. A follow-up assessment of mothers and infants takes place at home when the infants are 6 months old (corrected age). At this time, the BSID-III is administered, in conjunction with observation of mother-infant interaction, and the completion of the same set of self-report measures used at baseline and at the immediate post-intervention assessment.

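### The plan wrongly says 46 mothers per group rules out multiple imputation, which leaves the unadjusted primary t-test a complete-case comparison by implication

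*Protocol article*

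**What the plan says.** All the analysis text is in the Planned analyses section of the protocol article.

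- The post-intervention STAI score "will be analyzed using an unpaired t-test (i.e. comparison of scores between two independent samples) and an intent-to-treat strategy". Later in the paragraph this intention-to-treat analysis is contrasted with an exploratory comparison by treatment actually received.
- A secondary analysis uses a "multiple regression model to account for other predictors of outcome, including baseline STAI, and the demographic variables noted immediately above". Those variables are maternal age, education, parity, psychosocial services used and infant illness severity.
- On missing data, giving the 46 mothers per group as the reason: "we cannot use sophisticated multiple imputation techniques to estimate expected results in subjects who withdraw from the study". As a consequence, "we will document and describe the reasons for attrition within each group, but exclude these subjects from the multiple regression analyses".

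No other method for missing outcomes is named, and the section does not say how mothers without a post-intervention score enter the t-test.

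Two other places bear on the point. The power paragraph under Participants asks for 40 per group and then says: "To account for attrition, a sample of 46 mothers per group will be recruited". Under Procedures, STAI, PPQ and EPDS are taken before randomization, and the 6-month visit includes "completion of the same set of self-report measures used at baseline and at the immediate post-intervention assessment".

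**The concern.** This is a missing-data rule with a reason attached, so it is not a detail left to a later analysis plan. A later plan that used imputation would have to contradict it.

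The reason does not hold. No minimum sample size for multiple imputation excludes 46 per arm; a small sample only limits how many variables the imputation model can carry. The same paragraph treats the sample as large enough for a regression on baseline STAI and five further variables. An imputation model needs no more than that and could use baseline STAI alone. A likelihood-based mixed model needs no imputation at all.

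With imputation ruled out and nothing put in its place, the primary t-test falls back on mothers who supplied the outcome. It also ignores baseline STAI, so it is the planned analysis most exposed to selective dropout. The document foresees attrition in the sample size, and among its reasons for the Care arm (Trial interventions) is limiting dropout from the control group. At stake is the size of the primary treatment difference.

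**Working it through.** **1. The plan's own figures.** Inputs from the document: difference 7 points, two-sided alpha 0.05, power 0.80, 40 per group, 46 recruited. No SD is given, so 40 cannot be strictly reproduced, but the formula can be solved for SD:

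n = 2(1.960 + 0.842)² SD² / 7², so SD = 7 / (2.802 × √(2/40)) = 11.17.

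SD 10 gives 33 per group, 11 gives 39, 11.17 gives 40 and 12 gives 47. The plan is therefore consistent with an SD of about 11. Implied attrition is 1 − 40/46 = 6/46 = 13.0%.

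**2. Does imputation work at 46 per arm?** Simulation with 46 per arm, normal outcome, SD 11.17, baseline-outcome correlation 0.5, true difference −7 (Cues minus Care) and 2000 replicates. Dropout is logistic in standardised baseline STAI, with slope 0, +1 or −1 per SD. Imputation is by normal regression on baseline STAI within arm, with 20 imputations, Rubin's rules and small-sample degrees of freedom. The SD, correlation and dropout patterns are assumptions. Each cell shows bias in points and 95% interval coverage.

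| Dropout Care / Cues | Slope Care / Cues | Complete-case t-test | Imputation | Complete-case regression on arm and baseline |
|---|---|---|---|---|
| 13% / 13% | 0 / 0 | 0.02; 94.9% | 0.01; 95.3% | 0.04; 95.3% |
| 13% / 13% | +1 / +1 | 0.02; 95.1% | 0.01; 95.4% | 0.01; 95.0% |
| 5% / 21% | +1 / +1 | −0.76; 94.5% | 0.01; 95.4% | 0.05; 95.0% |
| 5% / 21% | 0 / +1 | −1.00; 93.2% | 0.01; 95.8% | −0.02; 95.3% |
| 13% / 13% | −1 / +1 | −1.25; 92.7% | 0.04; 95.1% | 0.02; 94.7% |

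Simulation error is about 2.5/√2000 = 0.06 points for bias and √(0.95 × 0.05/2000) = 0.5 percentage points for coverage. The imputation biases are therefore indistinguishable from zero, and the t-test's 94.5% is within about one simulation error of 95%.

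**3. A second set-up.** With SD 11, correlation 0.5, true difference 0, 13% dropout in each arm and 4000 replicates, the complete-case t-test is biased by 0.67 points when dropout rises with baseline anxiety in one arm only, and by 1.31 when it acts in opposite directions. Analyses conditioning on baseline STAI were biased by 0.01 to 0.05.

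**4. Scale.** The extremes across both set-ups are 0.67/7 = 10% and 1.31/7 = 19% of the 7-point difference. With 40 per arm and SD 11, the standard error is 11 × √(2/40) = 2.46, so these are 0.27 and 0.53 standard errors.

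**5. Precision.** Across the five scenarios in step 2, the SD of the estimate was 2.45 to 2.50 for the t-test, 2.44 to 2.51 for imputation followed by an unadjusted comparison, and 2.13 to 2.20 for the baseline-adjusted regression. The precision gain comes from adjusting for baseline, not from imputing.

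**6. Dropout that depends on the unseen score.** If mothers missing from one arm differ from completers by k points, the complete-case difference moves by 0.13 × k: 0.46 for k = 3.5, 0.91 for k = 7 and 1.45 for k = 11.17. Neither a mixed model nor standard imputation removes this shift.

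**The case against.** A reader might infer that the document contradicts itself by promising intention-to-treat and then removing withdrawn mothers from the primary analysis. The text does not go that far. The exclusion is written only for the multiple regression analyses, which are secondary. The contrast with treatment actually received suggests that intent-to-treat here means analysed as randomized. That the t-test is complete-case follows by implication, because a t-test needs an observed score and no method supplies one.

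A reader might also infer that the written exclusion itself biases the results. Under the simulated mechanism it hardly does: the regression it applies to includes baseline STAI and was within 0.05 points of the truth. The 0.7 to 1.3 points belong to the unadjusted t-test. They also need dropout related to baseline anxiety differently by arm, and nothing in the document shows that this will occur. The plan takes steps against attrition: a matched control contact schedule, exclusion of infants likely to leave within 4 weeks, work with transfer coordinators and reporting of reasons by group.

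Two further inferences are unsupported. Nothing says that mothers who stop sessions lose outcome collection; the text concerns withdrawal from the study. Nor can it be said how much usable 6-month data would be lost, since mothers who withdraw may give no 6-month score.

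These objections narrow the point and lower its severity. They do not rescue the stated reason for rejecting imputation, and they leave the more exposed analysis as the primary one.

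**Conclusion.** The point holds in limited form and should be fixed. The claim that 46 per group prevents multiple imputation is wrong, and it leaves the primary t-test as a complete-case comparison by implication. At 13% attrition the possible bias is roughly 0.7 to 1.3 STAI points if dropout depends on baseline anxiety differently by arm, with coverage of 92.7% to 94.5% in the affected scenarios of the first set-up. That is a risk and not a prediction: it rests on an assumed SD of about 11, a correlation of 0.5 and an assumed dropout pattern, and its direction would reverse if the pattern were reversed between arms. With random or similar dropout in both arms the t-test is unbiased, and the planned baseline-adjusted regression is nearly unbiased when missingness depends only on baseline STAI.

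**What to change.** 1. Delete the statement that multiple imputation cannot be used, and say how missing post-intervention STAI scores enter the primary analysis.
2. Make the primary post-intervention contrast a baseline-STAI-adjusted analysis of all randomized mothers, using data already collected. One option is a linear mixed model for the post-intervention and 6-month STAI with arm, visit, arm-by-visit and hospital. Treating baseline STAI as a further response with a common mean across arms keeps in mothers who have only a baseline score. The other option is a small imputation model by arm using baseline STAI, followed by a baseline-adjusted comparison.
3. Keep the complete-case t-test as a sensitivity analysis.
4. Add one sensitivity analysis for data not missing at random, such as shifting the imputed scores in one arm over a stated range.

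The cost is revised wording and modest extra programming, with no new data. The new primary analysis rests on a missing-at-random assumption, which is why item 4 is needed. The choice should be fixed before outcome data are examined by arm.

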### Safety

The Cues and Care programs are psychosocial interventions, so there are no medical risks to either mother or infant. Mothers may find that the completion of questionnaires asking about anxiety and stress may arouse feelings of distress, though this has not been a problem in pilot work; those who experience such distress will be offered a consultation with one of the clinical psychologists affiliated with the trial, who may then refer them to appropriate services as needed. In addition, all mothers who score above the cut point for depression on the EPDS are offered a referral for evaluation by a mental health professional.

